##### Numeric rating scale (NRS)

2.4.2.2

NRS is a numeric pain scale for an objective assessment of subjective pain felt by patients.^[16,18]^ The patient selects the appropriate point, with no pain as 0 and the worst pain possible as 10. The level of pain felt by the patient on movement and at rest will be assessed.

NRS will be measured 6 times in total; at the baseline, the last visit of each week during the intervention period (visits 4 and 7), week 3 (visit 8), and week 8 (visit 9).

##### Vernon-Mior neck disability index (NDI)

2.4.2.3

NDI is an assessment tool for disabilities caused by neck pain while performing daily activities and consists of 10 items. Scores from 0 to 5 can be selected for each item, allowing for a total score of 50 points. The higher the score, the greater the disability in daily living.^[19,20]^

NDI will be measured 6 times in total; at the baseline, the last visit of each week during the intervention period (visits 4 and 7), week 3 (visit 8), and week 8 (visit 9).

##### Northwick park neck pain questionnaire (NPQ)

2.4.2.4

The NPQ is a questionnaire that consists of 9-question items on daily life activities affected by the neck pain (intensity, sleep, numbness, duration, carrying things, reading/watching TV, working, social activities, and driving). Each question consists of 5 levels with 0 to 4 points, and a higher score indicates more severe consequent patient disabilities.^[21]^ In this study, the Korean version of the NPQ, translated and validated by Lee at al, will be used.^[22]^

NPQ will be measured 3 times in total; at the baseline, week 3 (visit 8), and week 8 (visit 9).

##### Patient global impression of change (PGIC)

2.4.2.5

PGIC is a scale that assesses the patient's perception of improvement in 7 stages, and the subject responds to the improvement in functional limitations after treatment with a 7-point Likert scale. (1 = very much improved, 2 = much improved, 3 = minimally improved, 4 = no change, 5 = minimally worse, 6 = much worse, and 7 = very much worse). This assessment scale was originally developed for psychological purposes but is currently used in other medical fields for assessing the improvement of pain.^[23]^

PGIC will be measured twice in total; at week 3 (visit 8) and week 8 (visit 9).

##### Credibility and expectancy

2.4.2.6

For the assessment of the expectancy for treatment of the patients, a 9-point Likert scale will be used.

During the first visit at Week 1 (baseline), the subjects will select a score in response to a question “How much do you think the treatment you receive during the clinical trial period will relieve your symptoms?” (1 = almost no expectancy, 5 = moderate, and 9 = highly expectant).

##### Physical examination, ROM

2.4.2.7

Muscle weakness and loss of sensation will be examined and recorded. The active ROMs for the neck for flexion, extension, lateral flexion, and rotation will also be measured. In addition, the pain and discomfort status during each movement will be measured and recorded.

Physical examination and measurement of ROM will be performed 6 times in total; at the baseline, the last visit of each week during the intervention period (visits 4 and 7), week 3 (visit 8), and week 8 (visit 9).

##### Five-Level EuroQol 5-dimension (EQ-5D-5L)

2.4.2.8

EQ-5D indirectly estimates the quality weight of a specific health condition through a survey of the health condition through multiple aspects. It is the most widely used tool for assessing the quality of life. EQ-5D-5L is composed of 5 items (mobility, self-care, usual activities, pain, and anxiety/depression) that investigates the current health status. The subjects respond to the questions using the 5-point Likert scale. (1 = I have no problems about, 2 = I have slight problems about, 3 = I have moderate problems about, 4 = I have severe problems about, and 5 = I am unable to about) In this study, the Korean version EQ5D-5L will be used with its validity verified.^[24]^

EQ-5D-5L will be measured 3 times in total; at the baseline, week 3 (visit 8), and week 8 (visit 9).

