##### Twelve-Item short-form health survey (SF-12)

2.4.2.9

The SF-12 is a survey questionnaire that assesses the health-related quality of life. The SF-12 consists of 12 questions in 8 domains that evaluates the physical and mental health. Domains related to physical health include physical functioning, role physical, body pain, and general health, and domains related to mental health include vitality, social functioning, role-emotional, and mental health. The higher the score, the better the quality of life. In this study, the validated Korean version of the SF-12 will be used.^[25]^

SF-12 will be measured 3 times in total; at the baseline, week 3 (visit 8), and week 8 (visit 9).

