##### EuroQol visual analogue scale (EQ-VAS)

2.4.2.10

EQ-VAS is one of the tools that assess the quality of life. The patient can indicate their health condition along a continuous vertical line of 100 mm in length, with the bottom end indicating the worst health condition possible and the top end indicating the best health condition possible.^[26]^

EQ-VAS will be measured 3 times in total; at the baseline, week 3 (visit 8), and week 8 (visit 9).

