### Statistical analysis

2.11

This study will be a randomized controlled study that analyzes the pain intensity scale, functional scale, quality of life, and costs data results of patients who meet the selection criteria.

The primary analyses will be the intention-to-treat analysis, which evaluates those who have received treatment at least once, and the per-protocol analysis, which evaluates only those who have successfully completed the clinical study, excluding those who have been dropped out; the 2 analyses will be performed concurrently.

For processing the missing values, multiple imputations using the Markov Chain Monte Carlo method will be used as the primary method, and 20 imputed datasets will be generated. In addition, the last observation carried forward method will be used for the sensitivity analysis.

The sociodemographic characteristics and treatment expectancy of the subjects will be evaluated for each of the groups. Continuous variables will be represented as mean (standard deviation) or median (quartiles), and categorical variables will be represented as a frequency (%).

The effectiveness endpoint of this clinical trial will be the difference in the amount of change between baseline and each time point by the group for the continuous outcomes (NRS, VAS, NDI, NPQ, EQ-5D-5L, and SF-12). Analysis of Covariance will be performed using the baseline values of each variable as covariates and the group as a fixed factor.

For the sensitivity analysis, datasets without the imputed values will be used to analyze the degree of change from the baseline. The mixed-effects repeated measures analysis will be performed for the primary and secondary outcomes at all time points. The time variable will be included as a categorical variable and the interaction terms of group and time will be included at each time point to evaluate the difference in the effectiveness of MSAT.

To compare the total amount of difference between 2 groups for each outcome within the treatment period (2 weeks) and the entire study period (8 weeks), the areas under the curve (AUC) within each period after randomization will be calculated. The difference in AUC between the 2 groups will be compared using the independent student *t* test.

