Survival analysis for VAS of neck pain will be performed. At each time point, the patient ratio will be comparatively analyzed for each time point when the neck pain VAS falls below half of the baseline. A Kaplan–Meier survival analysis will be used to estimate the time until less than half of the neck pain recovery occurs after randomization, and the differences between groups will be compared using a log-rank test. Also, the Cox model will be used to estimate the hazard ratio.

All statistical analyses will be performed using the SAS version 9.4 statistical package (SAS Institute, Cary, NC) with the significance level set to *P* < .05. In addition, the analysis will be performed after the end of the study (when all patients follow-ups have been completed) and interim analysis will not be allowed.

In addition, this study aims to investigate the cost-effectiveness between MSAT and acupuncture treatment through an economic evaluation. The primary economic endpoint will be the incremental cost-effectiveness ratios of cost per Quality Adjusted Life Years (QALY) of the MSAT group against the acupuncture treatment group. The analysis period is the entire study period including the intervention period and follow-up period, and if estimation for the subsequent period is required, the costs and effectiveness after the follow-up period will be estimated by extrapolation through a regression model or a secondary analysis with decision modeling analysis.

Medical costs will be calculated based on the number of treatments and the unit cost. For the unit cost, data on health insurance costs, institutional cost data, and patient answers will be used. The quality of life estimation for the QALY calculation, the quality of life derived by EQ-5D-5L will be used as the main endpoint, and EQ-VAS, and SF-6D will be used for the sensitivity analysis. The AUC method will be used for calculation. The units for the costs will be unified in Korean currency (won) as of 2020 and a 5% discount rate will be applied based on the guidelines for the economic evaluation of the Health Insurance Review and Assessment Service and represented in US dollars using the published exchange rate.

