## Discussion

3

For spinal disease, the treatment that utilizes passive and active movements of the patient after needle insertion has gained recent widespread usage in China as well as in Korea.^[13,14]^ Liu et al^[28]^ and Lin et al^[29]^ reported greater improvements in pain and ROM in the MSAT group compared to the control group with other types of treatments such as loxoprofen, physical therapy, and conventional acupuncture in RCT for acute low back pain patients. Shin et al^[30]^ reported greater effective improvement of pain and physical functionality in the MSAT treatment group compared to the diclofenac injection group in their study with patients with severe, acute low back pain. Luo et al^[31]^ reported superior outcomes in the MSAT group compared to the conventional acupuncture treatment group in a short-term treatment in their clinical study on cervical spondylosis. In an RCT with 100 WAD patients from traffic accidents conducted by Kim et al,^[15]^ the group that underwent a combination of trapezius MSAT and integrative Korean medicine treatment demonstrated a faster pain reduction and ROM improvements than the group with integrative Korean medicine treatment alone. However, qualitative evidence for the effectiveness and safety of MSAT is still insufficient.

To our knowledge, this study is the first well-designed, multi-centered RCT that evaluates the effectiveness, safety, and cost-effectiveness of MSAT for acute neck pain. Due to the nature of the study design, the physician and patients cannot be blinded, but the outcome assessors and statistical analysts will be blinded to retain objectivity as much as possible.

The results of this study will be useful for clinicians in primary medical institutions, that are frequently visited by patients with acute neck pain, and for policymakers working in healthcare insurance.

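### EQ-5D-5L, NPQ and SF-12 have no value between baseline and week 3, so their planned 2-week AUC only restates the week-3 difference and the QALY can miss a utility difference during treatment

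*Protocol article*

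**What the plan says.** Section 2.4.2.8 sets the utility schedule: "EQ-5D-5L will be measured 3 times in total; at the baseline, week 3 (visit 8), and week 8 (visit 9". NPQ (section 2.4.2.4), SF-12 (2.4.2.9) and EQ-VAS (2.4.2.10) have the same three time points; for NPQ the text is "NPQ will be measured 3 times in total; at the baseline, week 3 (visit 8), and week 8 (visit 9".

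Other outcomes are sampled during treatment. NDI is taken at baseline and then at "the last visit of each week during the intervention period (visits 4 and 7), week 3 (visit 8), and week 8 (visit 9". VAS, NRS and ROM share those visits. Under section 2.4.2.11, productivity loss is also measured at visits 4 and 7, and medical costs at every visit.

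Section 2.11 names NPQ, EQ-5D-5L and SF-12 among the continuous outcomes and then introduces the AUC analysis: "To compare the total amount of difference between 2 groups for each outcome within the treatment period (2 weeks) and the entire study period". The arms are compared by an independent t test. The economic part of the same section makes cost per QALY the primary economic endpoint. EQ-5D-5L is the main source, with EQ-VAS and SF-6D as sensitivity analyses, and it adds: "The AUC method will be used for calculation".

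**The concern.** Two planned quantities rely on data that the schedule does not collect.

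The first is the 2-week AUC of NPQ, EQ-5D-5L and SF-12. It would be read as evidence about the treatment period, yet no value of these outcomes is taken during treatment.

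The second is the QALY. Section 2.4.2.8 describes EQ-5D-5L as recording current health, so the week-3 answer does not look back over the preceding weeks. Costs are collected throughout treatment while utility is not, so the two parts of the cost-per-QALY ratio are sampled unequally. Section 2.3.3 restricts other neck-pain treatment only up to the primary endpoint. The unsampled stretch is therefore the one in which the arms are compared most cleanly.

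**Working it through.** The plan gives no QALY or AUC figure, so there is nothing to reproduce on this point. Table 1 is not shown; the schedules below come from the text.

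**Inputs from the protocol.** EQ-5D-5L, NPQ and SF-12 at baseline, week 3 and week 8 only; treatment lasts 2 weeks; visits 4 and 7 close the two treatment weeks. Section 2.4.1 calls baseline Week 1, so week 3 may lie 3 or 2 weeks after baseline. Both are used.

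**2-week AUC.** Let U0 and U3 be a patient's scores at baseline and week 3.
- Week 3 at 3 weeks: the line passes through U0/3 + 2·U3/3 at week 2. AUC = ½·2·(U0 + U0/3 + 2·U3/3) = (4/3)·U0 + (2/3)·U3.
- Week 3 at 2 weeks: AUC = ½·2·(U0 + U3) = U0 + U3.

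With baseline equal or adjusted for, the arm difference is 2/3 or 1 times the week-3 difference. The planned t test does not adjust for baseline, so chance baseline imbalance also enters, but that carries no information about treatment.

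**QALY.** Let d(t) be the arm difference in utility, with d(0) = 0. On the planned grid, the part up to week 3 is ½·T·d(week 3), with T = 3 or 2 weeks. Nothing at visits 4 or 7 can enter.

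**Size, with assumed utility curves.** Peak difference 0.05; visits 4 and 7 at weeks 1 and 2; week 3 at 3 weeks; trapezoids in utility-weeks, divided by 52 for QALYs.
- A, converged by week 3 (0, 0.05, 0.025, 0, 0): five points 0.025 + 0.0375 + 0.0125 + 0 = 0.075, or 0.00144 QALY; planned grid 0.
- B, half remaining (0, 0.05, 0.05, 0.025, 0): five points 0.025 + 0.05 + 0.0375 + 0.0625 = 0.175, or 0.00337; planned 0.0375 + 0.0625 = 0.10, or 0.00192.
- C, all remaining (0, 0.05, 0.05, 0.05, 0): five points 0.025 + 0.05 + 0.05 + 0.125 = 0.25, or 0.00481; planned 0.075 + 0.125 = 0.20, or 0.00385.

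| Curve | QALY kept, week 3 at 3 weeks | QALY kept, week 3 at 2 weeks | 2-week AUC kept (3 weeks / 2 weeks) |
|---|---|---|---|
| A | 0% | 0% | 0% / 0% |
| B | 57% | 62% | 22% / 32% |
| C | 80% | 84% | 44% / 61% |

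The 2-week reading puts visits 4 and 7 at 0.7 and 1.7 weeks and the last visit at 7 weeks.

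**Variant.** Visits at days 5 and 12, difference 0.05 at both, 0.02 at day 21, 0 at week 8. Five points: 0.0175 + 0.05 + 1.3·(0.05 + 0.02)/2 + ½·5·0.02 = 0.163, or 0.0031 QALY. Planned: 0.03 + 0.05 = 0.08, or 0.0015 QALY. That keeps 49%. If instead the difference is zero by week 3, the five points give 0.10 (day 21) or 0.075 (day 14), that is 0.0019 or 0.0014 QALY, against 0 as planned.

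**Smooth curves.** If both arms recover exponentially to a common plateau, rates of 0.5 and 0.8 per week keep 80% of the true QALY difference on the planned grid. Rates of 1 and 2 keep 38%. Adding weeks 1 and 2 gives 107% and 99%.

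**Effect on the ratio.** For a fixed cost difference, cost per QALY is multiplied by 1/share: 1/0.84 = 1.19 up to 1/0.49 = 2.04 when 84% to 49% is kept.

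**The case against.** Three utility points over 8 weeks do give a calculable QALY, and no section contradicts that schedule. The trial is also planned around a difference that is present at week 3: that is the primary endpoint, and section 2.6 assumes an effect size of 0.55. That figure concerns pain, not utility, but nothing in the documents predicts convergence by week 3. If the difference persists, about 80% to 84% of the gain is kept. Early recovery is not lost to the trial as a whole, because VAS, NRS, NDI and ROM are taken at visits 4 and 7. Early work recovery enters through productivity costs. All of this stands.

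Four stronger readings are tempting, and the documents do not support them.
- **The QALY cannot show early benefit.** This is true only if the arms have converged by week 3.
- **Faster recovery is the trial's hypothesis.** The Discussion cites a trial in which the combined-treatment group "demonstrated a faster pain reduction and ROM improvements than the group with integrative Korean medicine treatment alone", but those were whiplash patients receiving MSAT with other care. No such hypothesis is stated here.
- **The cost-effectiveness answer will be wrong against MSAT.** This would need a cost excess for MSAT. Both arms plan the same number of sessions of similar length with the same needles, and no cost figure or threshold is given. The distortion can also go the other way: a difference that emerges only late in treatment would be overstated by the straight line.
- **A PGIC area is planned but impossible.** PGIC is not in section 2.11's list of continuous outcomes.

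The objection does not remove the conflict over the 2-week AUC. It also cannot be left to later analysis, because utilities that were not collected cannot be recovered.

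**Conclusion.** The point holds in limited form. As written, the 2-week AUC of NPQ, EQ-5D-5L and SF-12 has no post-baseline value inside its window, or one at its edge if week 3 is day 14. It repeats the week-3 comparison under another name. This follows from the schedule and needs no assumption beyond linear interpolation.

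For the QALY, the early gain is lost in full if the arms converge by week 3. In the assumed scenarios with a 0.05 peak, about 16% to 50% is lost when some or all of the difference remains. The smooth-curve check with the faster recovery loses 62%. The absolute loss is roughly 0.001 to 0.002 QALY. All utility figures are assumptions. These amounts matter only because the QALY difference over 8 weeks is itself small and is the denominator of the ratio. Whether a decision would change cannot be told from the documents.

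The planned sensitivity analyses do not cover the gap: EQ-VAS has the same schedule, and so does SF-12, if SF-6D is derived from it.

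**What to change.** - **Schedule:** add EQ-5D-5L and EQ-VAS at visits 4 and 7, and calculate the QALY AUC from baseline, visit 4, visit 7, week 3 and week 8. The cost is five items and one line scale at two visits where other questionnaires are already completed, a few minutes per patient. SF-6D, if derived from SF-12, stays on the three-point grid, which should be stated as a limitation of that sensitivity analysis.
- **Section 2.11:** limit the 2-week AUC to outcomes measured within the treatment period (VAS, NRS and NDI, and EQ-5D-5L once added), and drop it for NPQ and SF-12. This is one sentence and costs nothing.
- **Time axis:** state how many days after baseline week 3 falls. Section 2.4.1 places it at visit 8 and section 2.3.3 at visit 9. These must be reconciled, because the interval sets the weights in every AUC.

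If the extra questionnaires cannot be added, the second and third changes should still be made, and the straight-line assumption between baseline and week 3 should be reported as a limitation of the QALY.

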##### Twelve-Item short-form health survey (SF-12)

2.4.2.9

The SF-12 is a survey questionnaire that assesses the health-related quality of life. The SF-12 consists of 12 questions in 8 domains that evaluates the physical and mental health. Domains related to physical health include physical functioning, role physical, body pain, and general health, and domains related to mental health include vitality, social functioning, role-emotional, and mental health. The higher the score, the better the quality of life. In this study, the validated Korean version of the SF-12 will be used.^[25]^

SF-12 will be measured 3 times in total; at the baseline, week 3 (visit 8), and week 8 (visit 9).

##### EuroQol visual analogue scale (EQ-VAS)

2.4.2.10

EQ-VAS is one of the tools that assess the quality of life. The patient can indicate their health condition along a continuous vertical line of 100 mm in length, with the bottom end indicating the worst health condition possible and the top end indicating the best health condition possible.^[26]^

EQ-VAS will be measured 3 times in total; at the baseline, week 3 (visit 8), and week 8 (visit 9).

##### Economic evaluation

2.4.2.11

For the economic evaluation, medical costs, non-medical costs, and cost of loss of productivity will be measured. For evaluation of cost items, a separately developed structured questionnaire will be used. Medical costs include not only the formal medical expenses incurred when using medical services at medical institutions but also the informal medical expenses incurred such as purchasing health foods and medical devices. The expenses associated with the use of medical services, such as transport expenses, patient time expenses, and caregiving service expenses, will be categorized as non-medical expenses. The cost of loss of productivity refers to the cost of economic loss incurred by the inability to participate in labor due to the disease itself or premature death due to the disease. To calculate the loss of productivity costs, the Work Productivity and Activity Impairment Questionnaire (WPAI)^[27]^ will be used and will be converted to costs for use in the economic evaluation.

Medical costs will be measured every visit and productivity loss costs will be measured 4 times in total; at the last visit of each week during the intervention period (visits 4 and 7), week 3 (visit 8), and week 8 (visit 9).

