### Sample size estimation

2.6

To estimate the number of study subjects, the results of the unpublished pilot study was used. Based on the pilot study, the effect size of MSAT for patients with neck pain is 0.55. When estimating the number of samples while using the *t* test as the primary analysis, the result showed that 106 subjects in total (53 per group) will be required. However, since the analysis of covariance is the primary analysis in this study, using the correlation coefficient of the mean difference between the baseline value and primary endpoint calculated through the pilot study, 0.24, the corrected number of samples was determined to be 100. Considering a dropout rate of 20% and recruitment from 4 institutions, a total of 128 subjects (64 subjects per group) were calculated as the number of samples required to conduct the clinical trial.

The calculation was performed based on the assumption level of significance at α=0.05 (2-sided test) and 80% of the power of the test with type 2 error (β) at 0.2. G∗Power 3.1.9.7 was used to estimate the sample size.

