Considering the characteristics of non-parametric data, 95% CI of the incremental cost-effectiveness ratios of cost per QALY will be estimated using the bootstrapping technique. In addition, the probability that of MSAT being cost-effective will be examined using the cost-effectiveness acceptability curves graph according to the degree of willingness to pay. All analyses will be made for costs through the healthcare system and social perspectives.

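### The productivity questionnaire has no baseline measurement, so the productivity part of the societal cost comparison cannot be adjusted for each patient's own loss at entry (minor, a matter of precision)

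*Protocol article*

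**What the plan says.** Section 2.4.2.11 (Economic evaluation) values lost productivity with "the Work Productivity and Activity Impairment Questionnaire (WPAI"), converted to money. On timing, "productivity loss costs will be measured 4 times in total; at the last visit of each week during the intervention period (visits 4 and 7"), plus week 3 (visit 8) and week 8 (visit 9). The stated count of four matches the four occasions listed, and baseline is not one of them.

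Section 2.11 (Statistical analysis) makes cost per QALY the primary economic endpoint and adds: "All analyses will be made for costs through the healthcare system and social perspectives". Productivity cost therefore enters the societal incremental cost. The 95% interval of the ratio "will be estimated using the bootstrapping technique", and acceptability curves are planned. No covariate is named for costs.

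Other patient-reported scales do start at baseline. For example, "EQ-5D-5L will be measured 3 times in total; at the baseline, week 3 (visit 8), and week 8 (visit 9"). SF-12, EQ-VAS, NDI and NPQ also list a baseline. For the continuous effectiveness outcomes, section 2.11 plans that "Analysis of Covariance will be performed using the baseline values of each variable as covariates and the group as a fixed factor".

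**The concern.** The trial relies on baseline adjustment elsewhere: its effectiveness analyses use it, and section 2.6 reduces the required sample because of it. The productivity schedule rules out the same step for one cost component. Patients who already lose much work time at entry may go on losing more, whichever arm they join. In a trial of 128 patients the arms can differ by chance in that respect, and without a baseline value the analysis can neither show the difference nor remove its contribution. The result is a wider interval than necessary for societal incremental cost, and a noisier societal cost-effectiveness ratio and acceptability curve. A baseline value not collected at the time cannot be properly recovered at the analysis stage.

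**Working it through.** **1. Is the omission a slip in the text?** Several schedules in section 2.4 have a count that disagrees with its own list. VAS at rest, NRS, NDI and range of motion each state six measurements but list five (baseline, visits 4, 7, 8 and 9). For productivity, the count (4) and the list (visits 4, 7, 8, 9) agree. The text as written excludes baseline.

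**2. The plan's own use of baseline adjustment (section 2.6).** The inputs are that "the effect size of MSAT for patients with neck pain is 0.55", with "assumption level of significance at α=0.05 (2-sided test) and 80% of the power of the test", a correlation of 0.24 and 20% dropout.

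- t test, noncentral t with d = 0.55: 53 per group (power 0.801), so 106 in total. This reproduces.
- Covariance correction: 106 × (1 − 0.24²) = 106 × 0.9424 = 99.9, so 100. This reproduces, and it shows that 0.24 is used as the baseline to endpoint correlation.
- Dropout: 100 / (1 − 0.20) = 125. The next multiple of 8 (4 sites × 2 arms) is 128. This reproduces.

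The sample size is sound on its inputs and is not affected by this point. The step from 106 to 100 is the same 1 − ρ² gain that productivity cost forgoes.

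**3. Size of a chance imbalance at entry.** In SD units of baseline productivity loss, SE = √(2/n).

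- n = 64 per arm: √(2/64) = 0.177; 95% range ±1.96 × 0.177 = ±0.35 SD.
- n = 51 per arm (64 × 0.8 = 51.2, the planned dropout): √(2/51) = 0.198; 95% range ±0.39 SD.

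**4. What carries forward, and what adjustment would gain.** Let ρ be the correlation between baseline and follow-up productivity cost. The article does not give it. The rows below are assumptions, starting from 0.24, the article's only correlation, which is for pain. Variance removed = ρ²; SE reduction = 1 − √(1 − ρ²); equivalent total N = 128 / (1 − ρ²); shift in the follow-up difference from an imbalance at the 95% limit = ρ × 0.346 SD.

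| ρ (assumed) | Variance removed | SE reduction | Equivalent N (instead of 128) | Extra patients | Shift at 95% limit |
|---|---|---|---|---|---|
| 0.24 | 5.8% | 2.9% | 136 | 6% | 0.08 SD |
| 0.3 | 9% | 4.6% | 141 | 10% | 0.10 SD |
| 0.5 | 25% | 13.4% | 171 | 33% | 0.17 SD |
| 0.6 | 36% | 20% | 200 | 56% | 0.21 SD |

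**5. From productivity cost to societal cost.** Societal cost also contains medical and non-medical costs. Suppose productivity supplies a share w < 1 of the variance of societal cost, and the other components are unrelated to it and to the baseline value. Adjustment then removes w × ρ² of that variance, which is less than the table shows. The article gives no basis for w, so no figure is put on it.

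**The case against.** The strongest reply is that nothing here is wrong. The cost comparison covers the period after randomisation, and the four measurements fall within it. EQ-5D-5L needs a baseline because QALYs are computed as an area under the curve; costs do not. Randomisation keeps the unadjusted difference unbiased, the bootstrap already reflects chance imbalance, and cost covariates are commonly left to the analysis plan. Most of this stands, and it keeps the point minor. It does not remove the point, because an analysis plan cannot add a covariate that the stated schedule never collects.

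Three stronger readings are tempting, and the article does not support them:

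- **That the societal comparison cannot be adjusted for entry differences at all.** NDI, NPQ (which has an item on working), EQ-5D-5L and SF-12 are all taken at baseline and could serve as partial proxies. Only adjustment for baseline productivity loss itself is ruled out.
- **That productivity is the only cost component without a known pre-treatment level.** Section 2.4.2.11 gives no schedule for non-medical costs, and for medical costs says only that they are recorded at each visit.
- **That an imbalance passes in full into incremental cost and could reverse the conclusion.** Only ρ times the imbalance carries forward, and no calculation from the article shows a reversal.

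A strong correlation also cannot be presumed. The introduction calls acute neck pain self-limiting, and entry requires onset or worsening within one month, so loss at week 8 may relate only weakly to loss at entry. For that reason the range must start at 0.24. The 1 − ρ² formula is a linear-model result and only approximate for skewed costs. Finally, the visit schedule in Table 1 is not legible in the copy reviewed and should be checked, though it would not override the explicit sentence in the text.

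**Conclusion.** The point holds as a minor one. The stated schedule prevents adjustment of productivity cost for each patient's own loss at entry. The cost is precision in the productivity component, and through it in the societal-perspective analysis. There is no systematic bias, and neither the primary outcome nor the healthcare-system perspective is affected.

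For productivity cost alone, the forgone gain is about 6% of variance at ρ = 0.24 and 36% at ρ = 0.6, the same as about 6% to 56% more patients. For total societal cost it is smaller by an amount the article does not allow one to compute. The figures rest on an assumed correlation, 64 analysed per arm and a linear adjustment. At the low end the gain is slight (2.9% of the standard error), but so is the price of obtaining it.

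**What to change.** Add baseline to the productivity schedule in section 2.4.2.11, making five occasions, and align Table 1. Give the questionnaire at the existing baseline visit before the randomisation envelope is opened. Section 2.8 has it opened in front of the patient and section 2.9 states that patients are not blinded, so answers given later could be influenced by the allocation.

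In section 2.11, state that the baseline value is a covariate in the productivity and societal-cost comparison. Also state that the adjusted model is refitted in each bootstrap resample, so that the interval and the acceptability curve carry the gain. If missing costs are imputed, the baseline value should enter the imputation model too: under the present schedule, a patient who leaves before visit 4 has no productivity value at all.

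The cost is one short questionnaire at a visit that already takes place, and one covariate. The sample size and the treatment schedule do not change.
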